#### Study design

This is an open, multicentric, interventional, prospective, non-randomised clinical investigation in which 10 000 volunteers undergoing conventional breast screening examination will also undergo the MammoWave exam. Recruitment of volunteers will be performed at nine centres in different European countries: two Italian hospitals (IRCCS Policlinico San Martino, Genova; and Ospedale San Giovanni Battista—USL Umbria 2, Foligno), one Polish hospital (Pomeranian Medical University Hospital, Szczecin), two Portuguese centres (Champalimaud Foundation, Lisbon and Clínica [name] Ângelo, Lisbon), three Spanish hospitals (Hospital Universitario de Toledo, Toledo; Hospital Universitario Reina Sofía, Córdoba and Hospital General Universitario Morales Meseguer, Murcia) and one Swiss hospital (University Hospital, Zurich). The study (see figure 3) will be composed of two phases:

A preliminary phase is planned to validate and fine-tune the optimised MammoWave’s AI classification algorithm. During this phase, the initial cohort will consist of 500 women recruited from all participating clinical sites. In this preliminary stage, all asymptomatic volunteers will undergo conventional mammography and ultrasound (US) examinations at a minimum to ensure optimal diagnostic accuracy. Suspected cases will follow the standard site-specific pathways, which may include additional tests such as MRI and biopsy.During the second phase, the remaining 9500 women will be enrolled. If the MammoWave’s AI label is positive, an US examination will be conducted (in addition to conventional mammography), particularly for women with dense breasts (recall, as per the European Society of Breast Imaging (EUSOBI), recommendations for screening in dense breasts^38^), unless such examination has already been performed. Suspected cases will follow the standard site-specific pathways, which may include additional tests such as MRI and biopsy. After the enrolment of 3000 volunteers, an interim evaluation will be carried out.

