#### Hypothesis and objectives

The aim of this clinical study is to validate, prospectively, MammoWave’s AI-based classification algorithm. The hypothesis underlying this clinical study is that MammoWave’s AI-based classification algorithm achieves a sensitivity of over 75% and a specificity of over 90% in the detection of BC within the screening process of asymptomatic individuals currently enrolled in population-based screening programmes.

The primary objective of this study is to generate evidence in the detection of BC by using MammoWave, evaluating its sensitivity and specificity, having as reference standard the output of conventional breast examination path (ie, screening mammogram, integrated with other radiological/histological output when deemed necessary by the responsible Investigator).

The secondary objectives of the study are as follows:

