### Analysis

#### Number of participants

The maximum number of participants will be 10 000 (for all the sites). The sample size was determined using the Buderer approach,^40^ considering that (1) the primary objective of the study is to confirm that MammoWave reaches sensitivity >75% and specificity >90% in BC detection on 10 000 volunteers undergoing breast screening, (2) a two-tailed 95% CI for sensitivity and specificity (CI width=10) and (3) a prevalence of female BC detected due to screening of 0.92%, according to the official English statistics of the National Health Service (NHS) Breast Screening Programme.^41^ A minimum of 8000 participants is required to reach the primary endpoint.

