#### Datasets

For the analysis, the following datasets for specific populations have been defined: safety set (SAF), which corresponds to all study volunteers who undergo MammoWave examination; full analysis set (FAS), which includes all volunteers who undergo MammoWave examination and have an evaluable result for the primary endpoint and per-protocol set (PPS), which includes all volunteers who do not have significant CIP violations that regard inclusion/exclusion criteria or that can condition efficacy evaluations.

The primary analyses on both primary and secondary outcomes (except safety evaluation) will be performed on the FAS. The analyses on the PP population will be performed if the PP population differs from the FAS by at least 5% and will be considered supportive of the analyses on the FAS population (sensitivity analysis). The safety and tolerability analyses will be performed on the SAF.

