#### Statistical considerations

Data from study participants will be analysed with descriptive statistics (mean, median SD, IQR, min/max for numerical variables, with frequency tables for categorical ones, percentages), 95% CIs as appropriate and graphical analysis on both the entire population and by strata (ie, dense/no dense breast) at the interim analysis and the end of the study. All the methods adopted for the statistical analyses will be described in the statistical analysis plan (SAP), to be issued before the interim analysis. The SAP will include a dedicated section in which the interim analyses are described. We anticipate that, within the interim analysis, sensitivity and specificity will be evaluated. In case the lower limit of the 95% CI is lower than 60% for the sensitivity or 70% for the specificity, the classification algorithm will be updated; otherwise, the study will continue without any modification.

All analyses will be conducted by using SAS (SAS Institute) V.9.4.

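### The primary analysis pools women labelled by up to three algorithm versions, so it need not estimate the performance of the version being validated

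*Protocol article*

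**What the plan says.** Hypothesis and objectives: "The aim of this clinical study is to validate, prospectively", the AI-based classifier. Number of participants describes the same purpose over the whole 10 000: "the primary objective of the study is to confirm that MammoWave reaches sensitivity >75% and specificity >90% in BC detection".

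Study design splits the 10 000 into two phases. For the first 500 women, "A preliminary phase is planned to validate and fine-tune the optimised" classifier; the other 9500 follow. An evaluation takes place once 3000 have been enrolled.

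Statistical considerations sets the interim rule. If the lower 95% limit is under 60% for sensitivity or 70% for specificity, "the classification algorithm will be updated; otherwise, the study will continue without any modification".

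Datasets defines the full analysis set (FAS) as every scanned woman whose primary endpoint is evaluable, and states: "The primary analyses on both primary and secondary outcomes (except safety evaluation) will be performed on the FAS". Neither phase 1 women nor women scanned before an update are set apart.

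Study design also says that the label produced once the scan is complete is the one carried to the final analysis. It separately describes re-evaluation with a further refined algorithm after the study. Study outcomes lists the results of that re-evaluation as secondary.

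**The concern.** A validation estimate should belong to one identifiable version of the device. Here the version may change after woman 500 and again after woman 3000, while the primary set runs from the first woman to the last. With scan-time labels, the reported sensitivity is a weighted average over versions, with weights set by when the changes happened. A result above or below 75% would then not show whether the final version meets the target. The pooled count would also hide how few women were scanned with that version.

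**Working it through.** **Inputs.** From Number of participants: target sensitivity 75%, "a prevalence of female BC detected due to screening of 0.92" per cent, "a two-tailed 95% CI for sensitivity and specificity (CI width=10" points), minimum 8000, maximum 10 000. From Study design: 500, 9500 and 3000 women. From Statistical considerations: limits of 60% and 70%. I count the 3000 from the start of enrolment; if they are counted within phase 2, fewer women remain afterwards.

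**1. The plan's own figure.** Buderer: N = z² × Se × (1 − Se) / (W² × prevalence).
- W = 0.10 as a half-width: 1.96² × 0.1875 / 0.01 = 72.03 cancers; 72.03 / 0.0092 = 7829 women (7935 if rounded up to 73 cancers). This reproduces 8000 to within 3%.
- W = 0.05 (10 points as full width): 288.1 cancers, 31 316 women. This does not reproduce 8000.

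So the plan's working precision is ±10 points. Specificity needs only about 35 women at W = 0.10, so sensitivity drives the size.

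**2. Expected cancers by version, if both changes occur.**

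| Women | Version | Expected cancers | Share |
|---|---|---|---|
| 1–500 | starting | 500 × 0.0092 = 4.6 | 5% |
| 501–3000 | after fine-tuning | 2500 × 0.0092 = 23.0 | 25% |
| 3001–10 000 | after interim update | 7000 × 0.0092 = 64.4 | 70% |

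**3. How likely is the interim update?** At the interim, 3000 × 0.0092 = 27.6 cancers are expected; take 28. A lower limit of at least 60% needs 22 detected (Wald or Wilson) or 23 (Clopper-Pearson). The chance of an update is the binomial probability of at most 21, or at most 22, detected out of 28.

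| True sensitivity | Wald/Wilson | Clopper-Pearson |
|---|---|---|
| 75% | 57.2% | 73.6% |
| 80% | 32.2% | 49.9% |
| 85% | 11.5% | 23.5% |
| 90% | 1.8% | 5.5% |

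The specificity limb hardly contributes for a device at its target: at 90% specificity the half-width with 3000 women is about 1.1 points, so the lower limit is near 89%.

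**4. Direction of the error with scan-time labels.** Treat the first 3000 as one group: pooled sensitivity = 0.30 × early + 0.70 × late. The values below are assumptions.
- Update helps, 60% early and 80% late: 0.30 × 60 + 0.70 × 80 = 74%. The final version exceeds 75%, but the pooled figure does not.
- Update harms, 70% early and 65% late: 0.30 × 70 + 0.70 × 65 = 66.5%, above the final version's 65%.

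A sensitivity-triggered update requires at most 21/28 (75%) or 22/28 (79%) detected early, so a downward error is the likelier case if the update works. For phase 1 alone, a 20-point difference between versions moves the pooled figure by 0.05 × 20 = 1 point.

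**5. Precision for a single locked version.** Half-width = 1.96 × √(0.1875 / cancers), at 75% sensitivity.
- All 10 000: 92.0 cancers, ±8.8 points.
- Without the 500: 9500 women, 87.4 cancers, ±9.1 points.
- After an interim update: 7000 women, 64.4 cancers, ±10.6 points.

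Keeping 8000 women after an update at 3000 would need 3000 + 8000 = 11 000 enrolled, above the stated maximum.

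**The case against.** A reader might infer something stronger: that the women used to tune the algorithm are scored by the version tuned on them, so the validation is inflated by its own training data. If early women showed 90% to 95% apparent sensitivity and the true value were 70% (assumptions), the pooled figure would be 0.30 × 90 + 0.70 × 70 = 76.0% to 0.30 × 95 + 0.70 × 70 = 77.5%, above the 75% target. The article does not support this reading. It carries the scan-time label to the final analysis, and the only re-scoring it describes comes after the study as a secondary outcome. It also does not say which data would feed an interim update; use of the 3000 would be an inference. Optimism would arise only if early women were relabelled for the primary analysis.

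Three further points on the other side are fair. The 500 carry only 5% of expected cancers. The precision lost after an update is modest, ±10.6 against the planned ±10. And a SAP section on the interim is promised, which may deal with versions.

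The first two limit the size of the problem. The third does not remove it: the article itself fixes the primary set as all evaluable women, so a SAP that restricted the set by version would depart from the stated rule.

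**Conclusion.** The point holds as a matter of what the primary result estimates. As written, the primary sensitivity and specificity can combine up to three algorithm versions and need not describe the final one. It is not shown that the result would be inflated: the sign depends on what the update does, and downward is likelier if the update helps.

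The fine-tuning phase is a small contributor. The interim update matters more, because a device exactly at 75% sensitivity is more likely than not to be changed (57% to 74%). It would leave at most about 7000 women on the final version, under the plan's own 8000. These figures rest on 0.92% prevalence, about 28 reference-positive cases being available at the interim, and binomial sampling.

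**What to change.** Define the primary analysis set as women scanned after the last change to the algorithm, with labels from that single locked version. Report phase 1 women, and any other women scanned before an update, separately by version. Keep the pooled all-women result as supportive.

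State the resulting precision in advance: 9500 women, about 87 cancers and ±9.1 points with no interim update; at most about 7000 women, 64 cancers and ±10.6 points if the update fires, and fewer if enrolment continues while the interim is carried out. Acknowledge that the second case is below the 8000 minimum.

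Settle this before the interim results are seen, since a set chosen afterwards would not be confirmatory. The cost is a change of protocol and SAP wording and a slightly wider confidence interval, with no added participants or procedures.

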**Figure 3 F3:**
[figure not shown]
Study design and recruitment process. AI, artificial intelligence; BC, breast cancer; DBT, digital breast tomosynthesis; DM, digital mammography.

Women attending the centres for their scheduled mammogram appointment (or those who have had a mammogram within the past month) will receive information about the study and will be invited to participate on a voluntary base. Women who agree to participate, meet the inclusion and exclusion criteria and sign their informed consent document will undergo the MammoWave examination. All the eligible women will be enrolled consecutively. The reason for non-participating in the study (fear of the new exam, lack of time, lack of information, lost-to-follow-up, breasts size larger than MammoWave’s cup) will be recorded by the investigators.

On completion of MammoWave’s scan of each breast, the data will undergo processing in a cloud platform to enable real-time and high-speed data processing. The output from MammoWave will primarily consist of microwave images (along with parameters that characterise these images) and will include the label generated by the novel AI-based classification algorithm; the label will be then used for final analysis by comparing it with conventional imaging results. Thus, the microwave images (which lack detailed morphological definition) and their associated features will not serve as a basis for diagnostic decisions made by radiologists or investigators.

Regarding intervention, if MammoWave’s results (ie, labels provided by its AI classification system) indicate WSF and there is a disagreement between MammoWave output and conventional mammographic imaging, additional examinations may be warranted. These may include US, if not already conducted, particularly for dense breasts, aligning with EUSOBI recommendations due to the reduced sensitivity of conventional mammography in dense breasts.^38^ All output information, including MammoWave’s results and conventional breast examination findings, will be collected and incorporated into this study. At each site, the investigators will prospectively compare MammoWave labels with the reference standard. Furthermore, on the study’s conclusion, the MammoWave labels will undergo centralised review by blinded specialists who will not have access to the reference standard. This review aims to validate the AI-produced data.

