#### Choice of comparator/control intervention

MammoWave’s results (labels provided by its AI-based classification algorithm) will undergo validation against a reference standard, which represents the output of the conventional breast examination pathway. This pathway includes screening mammograms conducted with DM or DBT, integrated with other radiological/histological findings as required by the responsible investigator, following the site’s ongoing procedures and clinical circuit. The reference standard’s results will be categorised as ‘positive’ when BC presence is confirmed by histology (ie, BI-RADS 6), otherwise labelled as ‘negative’ (BI-RADS 1, 2 or 3). Specifically, within this study BI-RADS 4 and BI-RADS 5 are only image suspicion criteria: when a biopsy is performed, they will be categorised as ‘positive’ when BC presence is confirmed by histology (ie, BI-RADS 6), otherwise labelled as ‘negative’ (BI-RADS 1, 2 or 3).

Conventional mammogram studies (2D or tomosynthesis) will adhere to approved protocols and clinical practices for breast screening. Radiological reports and interpretations will align with international guidelines, particularly those set by the ACR.^37^ The radiologists involved in this study will have extensive experience in mammographic interpretation, serving as the benchmark during the study. Details such as single or double screening readings and the utilisation of AI-assisted mammographic reading will be documented at each centre. Additionally, the integration of conventional mammogram studies with other radiological/histological findings will occur when deemed necessary by responsible investigators, who will record relevant variables in the electronic case report form (eCRF) following their usual clinical practice.

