#### Follow-up

The trial design will allow the comparative evaluation of both the conventional mammogram and MammoWave’s AI solution in terms of cancer detection rate, the number of recalls and positive predictive value, having as reference standard the 2-year follow-up of each volunteer. This follow-up allows to check retrospectively the possible rate of interval BC, and if this was reported as a false positive by MammoWave.

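### A positive MammoWave label triggers extra ultrasound in the second phase, and the reference standard is not consistently tied to 2-year follow-up, so sensitivity can be inflated

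*Protocol article*

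**What the plan says.** All references are to the protocol article.

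- **First phase (500 women), Study design.** Ultrasound does not depend on the label: "all asymptomatic volunteers will undergo conventional mammography and ultrasound (US) examinations at a minimum".
- **Second phase, Study design.** Here "the remaining 9500 women will be enrolled", and if MammoWave's "AI label is positive, an US examination will be conducted (in addition to conventional mammography), particularly for women with dense breasts", unless ultrasound has already been done. Nothing equivalent is stated for a negative label.
- **Intervention paragraph after Figure 3, Study design.** When a WSF label disagrees with mammography, "additional examinations may be warranted". This is weaker than the second-phase statement and has a different condition. The blinding paragraph adds that the MammoWave output goes automatically to the responsible investigator.
- **Choice of comparator/control intervention.** The reference standard is the conventional pathway, "integrated with other radiological/histological findings as required by the responsible investigator". A case is positive "when BC presence is confirmed by histology (ie, BI-RADS 6), otherwise labelled as" negative. Follow-up is not mentioned here, nor in the primary objective under Hypothesis and objectives.
- **Follow-up.** The comparison is made "having as reference standard the 2-year follow-up of each volunteer", in line with the Abstract and the strengths and limitations list. The section continues: "This follow-up allows to check retrospectively the possible rate of interval BC, and if this was reported as a false positive by MammoWave".
- **Study period.** The last enrolment is planned for February 2026 and the first evaluation for December 2026.

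**The concern.** The test under evaluation partly decides who is found to have the disease. A cancer that mammography misses can be found by the triggered ultrasound if MammoWave labelled the breast WSF, and it then counts as a true positive. The same cancer under an NSF label has no such route and stays a true negative unless it surfaces later. Each cancer found only through the trigger adds one to both the numerator and the denominator of sensitivity, while the matching misses enter only through follow-up.

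Whether follow-up restores the balance depends on which definition of the reference standard governs the primary outcome, and the sections differ. The one sentence on interval cancers names the false-positive side and does not say that an NSF woman with an interval cancer is a false negative. The primary hypothesis is a fixed threshold (sensitivity above 75%), so an uncorrected excess goes straight into the headline comparison.

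Ultrasound is also directed particularly to dense breasts. Ascertainment may therefore differ between the density strata in which detection rates are to be reported.

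**Working it through.** **1. The plan's own figure.** Number of participants uses the Buderer approach with sensitivity 75%, prevalence 0.92% and a 95% CI. Reading the stated width of 10 as ±10 points, 1.96² × 0.75 × 0.25 / 0.10² = 72.03 cancers, and 72.03 / 0.0092 = 7829 women (73 cancers: 7935). This agrees with the stated minimum of 8000. At 10 000 women, 92 cancers are expected, 87.4 of them in the second phase.

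**2. Follow-up available at the first evaluation.** Accrual runs from February 2024 to February 2026 (24 months). By December 2026 only women enrolled by December 2024 have 2 years of follow-up. With uniform accrual that is 10/24 = 42%.

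**3. Expected counts.** The following are assumptions, because the article gives no figures for them:

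- 92 mammography-detected cancers, 69 of them WSF (75%)
- *k* = 10, 20 or 30 occult cancers, half of them WSF
- triggered ultrasound finds 80% of the WSF ones
- follow-up captures a share *f* of all occult cancers not yet found, whatever the label
- for simplicity, the trigger applies to all women; the 500 first-phase women are 5% of the total

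True sensitivity = (69 + 0.5*k*) / (92 + *k*).

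Observed sensitivity = (69 + 0.5*k*(0.8 + 0.2*f*)) / (92 + 0.5*k*(0.8 + 0.2*f*) + 0.5*kf*).

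| *k* | True | Observed, *f* = 0 | *f* = 0.5 | *f* = 0.8 | *f* = 1 |
|---|---|---|---|---|---|
| 10 | 74/102 = 72.5% | 73/96 = 76.0% | 73.5/99 = 74.2% | 73.8/100.8 = 73.2% | 72.5% |
| 20 | 79/112 = 70.5% | 77/100 = 77.0% | 78/106 = 73.6% | 78.6/109.6 = 71.7% | 70.5% |
| 30 | 84/122 = 68.9% | 81/104 = 77.9% | 82.5/113 = 73.0% | 83.4/118.4 = 70.4% | 68.9% |

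The excess over true sensitivity is 3.5 to 9.0 points at *f* = 0, 1.7 to 4.2 at 0.5, 0.7 to 1.6 at 0.8, and zero at 1.

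**4. The part due to the trigger itself.** Without triggered ultrasound, observed sensitivity is (69 + 0.5*kf*) / (92 + *kf*). At *f* = 0 this is 69/92 = 75.0%, so the trigger adds 1.0 to 2.9 points. At *f* = 0.5 it adds 0.5 (74.2% against 71.5/97 = 73.7%) to 1.5 (73.0% against 76.5/107 = 71.5%). The rest of the excess arises because occult cancers, assumed harder for MammoWave, go uncounted.

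**5. Equal MammoWave sensitivity in both groups.** This model treats the first phase separately, keeps ultrasound yield at 80% and sets true sensitivity to 70%. For 1, 2 or 4 occult cancers per 1000, observed sensitivity is:

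- *f* = 0: 71.6%, 73.1%, 75.6%
- *f* = 0.5: 70.8%, 71.5%, 72.6%
- *f* = 0.8: 70.3%, 70.6%, 71.0%

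In this model an observed 75% corresponds to a true sensitivity between 69.4% (4 per 1000, *f* = 0) and 74.7% (1 per 1000, *f* = 0.8).

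**6. Can the sign reverse?** Yes. If MammoWave finds 90% of occult cancers against 75% of the others, and ultrasound finds half or fewer, the net bias at 4 per 1000 is −0.1 to −3.6 points.

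**The case against.** The strongest reply is that three places in the article name 2-year follow-up as the reference standard. Under that standard an NSF woman with cancer confirmed within 2 years is a false negative by definition, and with complete follow-up the bias is zero. This stands, and it is why the size depends so strongly on *f*. It does not settle the matter, because the two sections that define the reference standard for the primary objective and the comparator leave follow-up out, and the first evaluation comes before most women complete it.

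A reader might infer from the Follow-up section that interval cancers will be rescored in one direction only, from false positive to true positive. With 80% of them captured, such a rule would turn a true 70% into 71.7%, 73.3% or 75.9% at 1, 2 or 4 per 1000. The text does not support that reading. The sentence describes what follow-up makes possible, mentions the interval cancer rate as well, and follows directly on the statement that follow-up is the reference standard. It leaves the false-negative side unsaid; it does not rule it out.

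A reader might also infer that the bias decides the trial. That is not shown. With 92 cancers the 95% CI at 75% is about ±9 points (1.96 × √(0.75 × 0.25 / 92) = 0.088), and the article does not say that the claim rests on the point estimate.

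Two smaller replies also hold. Label-negative women may have ultrasound through site practice, so the contrast is not absolute. Detailed methods are left to the SAP, which is not at hand. However, the trigger and the conflicting reference-standard definitions are protocol statements.

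**Conclusion.** The point holds in this form: verification depends on the label in 95% of the cohort, and the article does not consistently state the one safeguard that would neutralise it. Relative to the same design without the trigger, the effect on sensitivity is upward whenever the trigger finds a cancer that would otherwise have gone uncounted. Relative to true sensitivity, it is upward if MammoWave is equally or less sensitive for occult cancers, and it can reverse if MammoWave is much more sensitive for them and ultrasound yield is low.

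The plausible size runs from under 1 point to about 4 points if follow-up captures 50% to 80% of the remaining occult cancers. It reaches 3.5 to 9.0 points only with no capture at all. These ranges rest on assumed occult-cancer numbers, ultrasound yield, MammoWave sensitivity for occult cancers and follow-up capture. The effect on specificity is negligible because few women change category. The matter should be corrected, but it does not invalidate the design.

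**What to change.** 1. Align Hypothesis and objectives and Choice of comparator with the Abstract, the strengths and limitations list and Follow-up. State that primary sensitivity is scored against 2-year follow-up for both label results: WSF with cancer is a true positive, NSF with cancer is a false negative.
2. Base the conclusion on the 75% threshold on women with completed follow-up, and call the December 2026 evaluation provisional. For the last women enrolled, 2 years end in February 2028.
3. Derive each cancer's detection route: mammography, WSF-triggered ultrasound only, or interval. Collected variables already lists screening BI-RADS, the MammoWave label, additional tests and biopsy outcomes, so the route at screening is largely derivable.
4. As a secondary sensitivity analysis, overall and by density, report sensitivity without the WSF-triggered-only cancers, and report those cancers separately as incremental yield. The claim should not rest on the lower of the two figures. With complete follow-up and the inputs of step 3, the exclusion gives (69 + 0.1*k*) / (92 + 0.6*k*) = 71.4%, 68.3% and 65.5% against true values of 72.5%, 70.5% and 68.9%. That is 1.1 to 3.4 points too low, because it drops detections while keeping every miss.
5. Reconcile the two Study design statements on when ultrasound follows a positive label.

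The cost is wording and one derived variable, with no added examinations. The downside is a somewhat lower headline sensitivity and a later definitive conclusion.
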